### Strategies to improve adherence to interventions {11c}

To improve adherence to the intervention protocols, routine visits will be made by monitors designated by the sponsor in order to check compliance with the protocol; the completeness, accuracy, and consistency of the data and adherence to Good Clinical Practice (GCP) requirements.

The principal investigator must ensure that electronic case report forms (e-CRFs) are completed in a timely manner and must allow periodical access to e-CRFs, patient records, drug logs, and all other study-related documents and materials.

The investigator will agree to provide laboratory assessment reports and results, and direct access to the subjects’ source data, which may exist in the form of hospital records, patient files, and notes.

### Relevant concomitant care permitted or prohibited during the trial {11d}

Throughout the duration of the study, the treatment regimen (medication or non-pharmacological therapies) will be kept stable whenever possible. In the case of a change, it will be traced in the e-CRF. Moreover, it is recommended that parents do not participate in other parental management training programs.

### Outcomes {12}

#### Primary endpoint

Change from baseline at 3 months of the Clinician-rated Affective Reactivity Index total score (CL-ARI) [26].

#### Secondary endpoints

Secondary efficacy endpoint at completion:Change from baseline to follow-up at 1 month of the program of the CL-ARI [26].

Secondary efficacy endpoints at 1 month and at 3 months follow-up:Change from baseline of the Clinical Global Impression Improvement (CGI-I) scale [27].Change from baseline in the Parenting and Familial Adjustment Scale (PAFAS) [28].Change from baseline of Parent-rated ARI (P-ARI) [29, 30] and Child-rated Cranky thermometers [31].

Exploratory efficacy endpoints and putative moderators and mediators:Initial score and change from baseline of specific Child Behavior Checklist (CBCL 6–18) (parent-rated) [32]: CBCL-internalizing, externalizing, and DP/Dysregulation short scale at 1 month (M1) and at 3 months (M3).Initial score of the personality dimensions assessed by parents (Hierarchical Personality Inventory for Children; HiPIC) [33]).Initial score and change from baseline of the parental expressed emotions and reflexivity rated with the Five-minute Speech Sample (FMSS) [34] at M3.Initial score and change from baseline in the Inventory of Callous Unemotional traits (ICU) [35].

Secondary acceptability endpoints:Observance.Acceptability (questionnaire for all parents and qualitative interview in a subsample of the ancillary RESIST-QUAL; the qualitative interview will be carried out after completion of the treatment).Discontinuation from the trial due to any cause and due to specific causes.

Other assessments:Socio-demographic and early development questionnaire.Medical history.Concomitant medications.K-SADS.Clinical Global Impression Severity (CGI-S) scale at baseline.

#### Pre-inclusion visit

The pre-inclusion visit can be done following a routine appointment in the centres or after a previous e-mail contact. The site investigator or clinician will give the family a first information about the research and hand out patient information and consent forms. An investigator from Montpellier will join the families by phone or videocall to answer further questions and check inclusion and exclusion criteria.

Informed consent and assent will be collected from parents, children and adolescents, before starting any trial-specific procedure through an online consent signature. Participants will be advised that research is entirely voluntary and that they can withdraw their participation at any time.

The centre will try to obtain consent from both parents. In case of consent from one parent only, this will be justified by the centre. The participation in the study remains possible for one parent.

At pre-inclusion, children are assessed to confirm their diagnostic status. This evaluation includes the Kiddie-Schedule for Affective Disorders and Schizophrenia (K-SADS) interview in the case it was not done in the 6 months prior to the pre-inclusion. The K-SADS is a semi-structured diagnostic interview designed to assess current and past episodes of psychopathology in children and adolescents according to DSM-5 criteria [36]. A french version has been finalized for DSM-5 diagnoses (download available at https://sfpeada.fr/k-sads-pl-dsm-5-version-francaise-2018/). Interviews will be carried out on site or online by trained master-level or doctorate-level clinicians.

At screening and during enrolment of the RESIST RCT, participants will be asked to maintain their current mental health treatment regimen for 4 weeks prior to the start of the program and through the second endpoint visit (e.g., second follow-up visit).

#### Baseline assessment: inclusion visit

After the signature of informed consent and verification of inclusion and exclusion criteria, the following baseline assessments will be completed by children and adolescents, parents, and clinicians by video-conference with the evaluator.

Parents’ assessments.Socio-demographic and early development questionnaire.Current medication status of the child.Hierarchical Personality Inventory for Children (HiPIC) [33].Parent-rated Affective Reactivity Index (P-ARI) [29].CBCL [32].Parental and Familial Adjustment Scales (PAFAS) [28].A short speech recording for the parental Expressed Emotion (EE) and reflexivity will be rated using the FMSS (putative mediator of treatment effect) [34].ICU [35].

Children’s/adolescents’ assessments.Cranky thermometers [31] (self-rated irritability with visual analogous scales).

Clinician’s assessments.Clinician-rated ARI (CL-ARI) [2].CGI-S [3].

#### Treatment groups

PMT and NVR online parent program sessions will be held by experienced clinicians from the University Hospital Centre (CHU) of Montpellier and will be open to clinicians from the recruitment sites for training purposes. The treatment programs are adapted from Barkley’s program for defiant children and teens [17, 37] and from the NRV program by [name] and [name], both of which are available as manuals [25].

The group sessions of each program are coordinated by two clinicians. Each session will include an open question period facilitated by the presence of a real time chat.

Format of the group therapy: 10 online sessions of either NVR of PMT with up to 60 participants over two consecutive days (5 sessions per day) with additional booster sessions at 1 and 3 months after the 10th session.

Both treatment groups will be led by a tandem of experienced clinicians (psychiatrists/psychologists/nurses/occupational therapists) from the coordinating centre at Child and Adolescent Psychological Medicine (MPEA1) of CHU Montpellier. One clinician leads the session and the oral discussions, while the other clinician monitors the chat and participates in guiding the discussion.

The NVR parent group format program consists of 10 sessions and 2 booster sessions designed to develop a positive form of authority based on parental presence, a parental support network, and strategies of non-violent responses in order to avoid escalation while promoting reconciliation gestures.

The PMT program consists of 10 sessions and 2 booster sessions. PMT is an evidence-based treatment for disruptive behavior disorders in which the child’s social environment is modified according to principles of operant conditioning and contingency management. The parental response to the child’s behavior increases or decreases the likelihood of targeted behavior.

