### Treatment as usual (TAU)

The TAU group receives non-pharmacological and pharmacological therapies as usually provided in the participating centres. The TAU group participates in the assessments as described in the procedures.

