## Methods

### Assignment of interventions (for controlled trials)

#### Allocation

##### Sequence generation {16a}

The randomization will be done with Ennov-Clinical software (CS-random module). The randomization will be centralized, available online, and stratified by minimization based on centre and on two age classes (6–11 and 12–15 years) and medication status (according to major classes of psychotropic), balanced with a 1:1:1 ratio. Each subject (i.e., here duo or trio of child and parents), who meets the eligibility criteria and signed informed consent, will be randomly assigned to one of the three study groups by the study investigator.

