#### Blinding

##### {17a}

After the signature of informed consent and verification of inclusion and exclusion criteria, the investigators involved in the assessments will be blinded to the type of program received by the parents. This aspect will be monitored throughout the study and parents will be instructed before every assessment to avoid disclosing the type of therapy received. Investigators will be different from the therapists involved in NRV and PMT.

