The comparability of our results from the different centres embedded in the RESIST RCT project will be enhanced by the webinar format of intervention therapies; the format will be delivered by the same set of instructors permitting the simultaneous participation of parents from different sites.

By organizing training of both PMT and NRV across major university centres, we hope to raise interest and develop skills in mental health professionals to use evidence-based psychotherapeutic approaches for children suffering severe mental health conditions.

In summary, a direct benefit is expected in both treatment groups for patients, parents, caregivers, and for the staff trained in the programs.

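### Site clinicians may attend the live PMT and NVR sessions with no limit on timing or role, although their centres provide TAU, so programme content can reach control families before the 3-month endpoint

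*Protocol article*

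**What the plan says.** Under Treatment groups, the online PMT and NVR sessions are run by clinicians of the coordinating centre and "will be open to clinicians from the recruitment sites for training purposes". No start date, end date or restriction by role is attached. The same section describes a live format with open questions and a real-time chat, for up to 60 participants per run.

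The comparator is defined under Treatment as usual (TAU): "The TAU group receives non-pharmacological and pharmacological therapies as usually provided in the participating centres". Under Sequence generation {16a}, the unit randomised is the child with one or both parents, and allocation is "stratified by minimization based on centre and on two age classes" as well as medication status. A centre's families are therefore meant to be spread over all three arms.

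Several provisions bear on contamination:
- Eligibility criteria {10} require a stable regimen, drug and non-drug, before inclusion and during the trial.
- Pre-inclusion visit asks families to keep their regimen through the second follow-up visit.
- Section {11d} says the regimen "will be kept stable whenever possible", with changes traced in the e-CRF, and "it is recommended that parents do not participate in other parental management training programs".
- Section {6b} offers TAU parents PMT or NVR in their own inclusion centre, but only after their last assessment.

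On blinding, Follow-up assessments and {17a} require blinded assessors, and {17a} adds: "Investigators will be different from the therapists involved in NRV and PMT". Clinicians who sit in on sessions are not mentioned. The Discussion adds a wider aim: "By organizing training of both PMT and NRV across major university centres, we hope to raise interest and develop skills in mental health professionals".

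**The concern.** The plan holds back programme access from TAU parents until their last assessment, but not from the clinicians who treat them. A clinician who attends an NVR or PMT run may then see a TAU family and pass on parts of what was taught. This can happen in an appointment that was already scheduled, so nothing need appear as a change of regimen.

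The direction of the bias is clear. If TAU families gain some of the programme effect, both primary contrasts (NVR against TAU, PMT against TAU) shrink, and a real benefit is understated or missed. The analysis could not readily correct this, because the article provides for recording neither which clinicians attended nor what TAU consisted of beyond regimen changes.

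There is a smaller, second issue. An attending site clinician may recognise a family and so learn its arm. The rule separating evaluators from therapists does not cover such a person.

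**Working it through.** **Does a route exist?** Four statements taken together:
1. Recruiting-site clinicians may attend (Treatment groups); no limit is stated.
2. Those centres supply the comparator (Treatment as usual).
3. Families are randomised individually and balanced within centre ({16a}), so one centre treats families of every arm.
4. More than one run per programme is needed. With 90 families per arm and at most 60 participants per run, 90 / 60 = 1.5, so at least two runs even if each family counts as one participant. A TAU family enrolled after an early run can meet staff who have already attended.

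The route follows from the text. Whether it is used, and how much, does not.

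**Inputs for the illustration** (Sample size {14}): expected change −2 in each active arm and −0.5 in TAU, difference d = 1.5, variance of means V = 0.5, SD 3, two-sided alpha 0.05, 77 evaluable per group.

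**Reproducing the plan's figure.** For means (−2, −2, −0.5) the deviations from the grand mean are −d/3, −d/3 and 2d/3, so V = 2d²/9 = 2 × 2.25 / 9 = 0.5. The omnibus F test has noncentrality λ = 3nV/SD² = 3 × 77 × 0.5 / 9 = 12.83 on 2 and 228 degrees of freedom. Power is 90.0%, so the stated 77 per group reproduces. For dropout, 77 / 0.85 = 90.6, against the stated 90; the gap is trivial and does not matter here.

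**Pairwise contrast with TAU.** Standard error = 3 × √(2/77) = 0.4835. Noncentrality = 1.5 / 0.4835 = 3.10 on 228 pooled degrees of freedom, giving 87.1% power. The drop from 90.0% to 87.1% reflects the choice of test and has nothing to do with contamination.

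**Adding leakage.** Let f be the share of the 1.5-point advantage that TAU families gain on average. Then d = 1.5(1 − f), with V and both noncentralities recomputed. The documents give no value for f; every row below the first is an assumption.

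| f (assumed) | d | V | Omnibus power | Pairwise power |
|---|---|---|---|---|
| 0 | 1.50 | 0.500 | 90.0% | 87.1% |
| 5% | 1.425 | 0.451 | 86.7% | 83.5% |
| 10% | 1.35 | 0.405 | 82.6% | 79.4% |
| 20% | 1.20 | 0.320 | 72.4% | 69.6% |
| 30% | 1.05 | 0.245 | 60.0% | 58.0% |

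Since f averages over all TAU families, it is the share treated by an attending clinician times the share of the effect passed on. For example, f = 10% needs about one third of TAU families treated by attendees who each transmit 30% of the effect (0.33 × 0.30 ≈ 0.10).

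**The case against.** The strongest reply is that the plan already restrains this. A stable non-drug regimen is an inclusion criterion, families are asked to keep it through the second follow-up visit, changes are recorded, parents are advised against other programmes, and TAU parents get theirs only after the last assessment. Follow-up lasts about three months, and a clinician who sat in on a session will not reproduce ten sessions of training. The Background also calls the Barkley programme the most common comparator therapy in France, and both programmes have manuals, so some PMT content may be in usual care whoever attends. All of this stands and limits the likely size; it leaves NVR as the more exposed contrast. It does not close the route. Stability applies only where possible, advice on other programmes is addressed to parents rather than clinicians, and new advice in an existing appointment need not count as a regimen change.

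Three stronger readings are tempting, and the documents do not support them:
- A reader might infer that the plan means to alter control care during follow-up. The Discussion says only "we hope to raise interest and develop skills in mental health professionals"; it gives no timing and does not mention TAU.
- A reader might infer that the primary evaluator is unblinded. Nothing says that site clinicians rate the CL-ARI. Baseline assessment has it done by video-conference with an evaluator whose affiliation is not given, assessors must be blinded, and parents are told not to disclose. What is missing is a rule that keeps attendees out of that role.
- A reader might take the lower rows of the table as a forecast. They are not; no leakage figure exists in the documents.

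**Conclusion.** The point holds as a design weakness of unknown size. The plan opens the experimental sessions to staff of the centres that deliver the comparator, within a trial randomised by family, and its safeguards reduce the resulting leakage without preventing it. Any leakage would pull both primary contrasts toward no difference, and the sample size makes no allowance for it. At an assumed 10% leak, power would be 82.6% (omnibus) or 79.4% (pairwise), given the plan's own difference, SD and 77 per group; at 5% the loss is about 3 to 4 points. The blinding part is a gap in the wording of {17a}, not a demonstrated breach. The change is worth making because it costs little, not because a large loss has been shown.

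**What to change.** - **Treatment groups:** state that, until a site's last TAU family has completed M3, only site clinicians who neither treat nor assess that site's randomised families may attend PMT or NVR sessions. Record who attended which run.
- **{17a}:** state that evaluators must differ from the therapists and from anyone who has attended a session.
- **{6b}:** reconcile the offer of training in the family's own inclusion centre with this restriction. Non-treating clinicians trained under the rule above, or the coordinating centre, can deliver it to TAU parents who finish early.

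Restricting by role is preferable to postponing all site training, which could leave a centre unable to honour the offer in {6b} to families who complete M3 first.

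The cost is an added sentence or two in each of the three places and an attendance log. Treating clinicians at each site are trained later, and the coordinating centre may have to take on some post-trial sessions. No additional participants are needed.

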#### Follow-up assessments

Investigators involved in assessments will be blinded as regards program/treatment status. A full assessment in parents and children will be completed at a 3 months follow-up.

At 1 month the following assessments are scheduled:

Parents’ assessments.P-ARI [29].CBCL [32].PAFAS [28].

Clinician’s assessments.CL-ARI [26].CGI-I [27].Observance of treatment sessions will be recorded by therapists involved in each treatment group.

Children’s/adolescents’ assessments.Cranky thermometers [31] (self-rated irritability with visual analogous scales).

At 3 months follow-up:

Parents’ assessments.P-ARI; specific irritability severity [29].CBCL [32].Parental EE and reflexivity will be rated using the FMSS (putative mediators of treatment effect) [34].HiPIC [33].PAFAS [28].ICU [35].Current medication status of the child.

Childrens’/adolescents’ assessments.Cranky thermometers [31] (self-rated irritability with visual analogous scales).

Clinician’s assessments.CL-ARI [26].CGI-I [27].

### Participant timeline {13}

The participation timeline of the RESIST protocol is represented in Fig. 1.

### Sample size {14}

According to the results of Maire [36] and Stringaris et al. [29], the mean score of ARI was 4.31 in an ADHD population with a standard deviation (SD) of 2.72, mean of 7.2 (SD 1.0) in severe irritability, mean of 5.1 (SD 1.5) in bipolar disorder, and mean of 0.5 (SD 0.2) in normal controls. In a recent study, a clinical sample had a mean of 3.5 (SD 1.4) and children with a diagnosis of disruptive mood dysregulation disorder had a mean of 4.9 (SD 1.4) [2]. In a clinical trial of online PMT, the mean ARI-irritability score decreased from 7.2 (SD 2.6) to 3.75 (SD 2.1) [42].

The mean expected improvement in each active group is −2 units. Among the control group (treatment as usual, TAU), the expected variation is −0.5. According to the One-Way analysis of variance (ANOVA) model in Nquery software, taking a difference between-group of 1.5 (Variance of means V = 0.5) with a SD of 3, a total sample size of 77 subjects in each group will permit detection of a difference between groups with a global two-sided alpha = 0.05 and with a power of 90%. Considering a dropout rate around 15%, it will be necessary to include 270 subjects (90 subjects/group).

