### Objectives {7}

The main objective of this study is to assess the impact of non-violent parenting resistance training (NVR) and standard parenting management training (PMT) versus “usual treatment” (TAU) in improving irritability in children and adolescents with a baseline parent-rated affective reactivity index (P-ARI) greater than or equal to 4 in the context of ADHD, ODD, CD, mood / anxiety disorders or DMDD at 3 months after the program completion.

Main study hypothesis:

Both NVR and PMT are superior to TAU in improving irritability between baseline and 3 months after the program completion.

The secondary objectives of this study are:Assess improvement of irritability at different time-points (e.g., post completion).Assess improvement of irritability according to different informants (e.g., parents, child).Assess improvement of parental strategies.Explore putative mediators of therapeutic effect (e.g., parental expressed emotion, co-occurring disorders, personality).Assess acceptability of the interventions.

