### Efficacy analyses

#### Primary endpoint

The full analysis set will be used for the primary endpoint.

The primary endpoint is the change from baseline (inclusion visit) at end of treatment (last visit) in the Clinician ARI total score. An analysis of variance will be performed to study the evolution of Clinician ARI total score (dependent variable) according to the three treatment groups and baseline value of ARI as a covariate. Each experimental group will be compared to the control group.

The treatment effect will be estimated by the least square mean (LSMean) of the difference with its two-sided 95% confidence interval. A graphical display of the LSMean and associated 95% confidence intervals for each treatment will be presented. In the event that marked deviations from the assumption of normality are observed, an additional analysis on the primary efficacy variable will be performed using non-parametric method.

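### The stated 90% power is for the omnibus three-group F test; the main hypothesis, that both NVR and PMT beat TAU, has about 79% power on the same inputs

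*Protocol article*

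**What the plan says.** Sample size {14} sizes the trial "According to the One-Way analysis of variance (ANOVA) model in Nquery software". For the active arms, "The mean expected improvement in each active group is −2 units"; for TAU, "the expected variation is −0.5". The stated inputs are a between-group difference of 1.5, a variance of means of 0.5 and an SD of 3. The result is 77 subjects per group for "detection of a difference between groups with a global two-sided alpha = 0.05 and with a power of 90" percent.

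Objectives {7} gives the main hypothesis: "Both NVR and PMT are superior to TAU in improving irritability between baseline and 3 months after the program completion".

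The Primary endpoint paragraph under Efficacy analyses plans an analysis of variance on the three groups with baseline ARI as covariate, and adds: "Each experimental group will be compared to the control group". Effects are reported as least-squares mean differences with two-sided 95% confidence intervals.

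The article gives no power for the two comparisons with TAU. It does not say whether one or both must succeed, and it does not say whether they are tested only after a significant overall F test.

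**The concern.** The sample size and the main hypothesis concern different tests. A significant F test on 2 degrees of freedom says only that the three means are not all equal. It can be significant when one programme separates clearly from TAU and the other does not. The main hypothesis needs two separate demonstrations against TAU, which is harder to achieve than a significant F.

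A reader who puts the 90% beside the main hypothesis will take the chance of missing that hypothesis, if the assumed effects are true, to be 10%. If it is materially higher, a result in which only one programme reaches significance is more likely than the article suggests, and it could be misread as evidence that the other programme does not work.

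**Working it through.** **Inputs.** All come from Sample size {14}: mean changes of −2 (NVR), −2 (PMT) and −0.5 (TAU); SD 3; 77 evaluable per group; two-sided alpha 0.05. No gain from the baseline covariate is assumed.

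**Step 1: reproduce the plan's figure.**
- Grand mean = (−2 − 2 − 0.5)/3 = −1.5.
- V = [(−0.5)² + (−0.5)² + 1²]/3 = 0.5, as stated.
- Noncentrality λ = n·k·V/SD² = 77 × 3 × 0.5/9 = 12.83, with 2 and 3 × 76 = 228 degrees of freedom.
- Noncentral F power at 5% = 90.03%. With 76 per group it is 89.6%.

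So 77 is exactly the smallest group size giving 90% for the omnibus F test. The sizing contains no arithmetic error.

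**Step 2: one comparison with TAU.**
- Noncentrality = 1.5/(3 × √(2/77)) = 3.10.
- Power ≈ Φ(3.10 − 1.96) = Φ(1.14) = 87.3%. The noncentral t with pooled error gives 87.1%.

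**Step 3: both comparisons.** The two test statistics share the TAU arm, so with equal groups their correlation is 0.5.
- The probability that both exceed 1.96 is 79.2% (bivariate normal).
- A simulation of 400,000 trials with estimated variance gives 78.8%.
- The probability of missing at least one is therefore about 21%.

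**Step 4: if the comparisons are read only after a significant F (same simulation).**
- Each: 84.2%. Both: 78.4%.
- Share of trials with a significant F in which the two-part hypothesis is not shown: 1 − 0.784/0.901 ≈ 13%.

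**Step 5: error rate and matching power under each success rule.**

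| Success rule | Type I error of the claim | Power at 77 per group |
|---|---|---|
| Both must succeed, 5% each | at most 5%, no adjustment | about 79% |
| Either suffices, no gate, 5% each | 9.07% if neither programme works | about 95% for at least one |
| Either suffices, gated by F | 4.2% if neither programme works (simulated) | about 90% for at least one; 84% each |
| Either suffices, Dunnett (about 0.027 each) | 5% | 81% each; 71% both |

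With three groups, testing the F first and then each comparison at 5% is a closed procedure. The family-wise error therefore also stays at or below 5% when only one programme works.

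**Step 6: sensitivity to the SD.** Baseline adjustment would reduce the residual SD if SD 3 is the unadjusted SD of change, which the article does not say. At 77 per group:

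| Residual SD | Each comparison | Both |
|---|---|---|
| 3.00 | 87% | 79% |
| 2.75 | 92% | 87% |
| 2.63 | 94% | 90% |

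Since residual SD = 3√(1 − ρ²), a residual SD of 2.63 needs a correlation between baseline and change of about √(1 − (2.63/3)²) = 0.48. The documents give no value for this correlation.

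**The case against.** The strongest defence is that the Sample size section is accurate as written. It names the one-way ANOVA, speaks only of a difference between groups, and calls alpha global; all of that describes an F test. It does not attach the 90% to the two comparisons. This stands to the extent that 77 is not a miscalculation. It does not remove the gap, because no other power is given and the hypothesis the trial exists to test is the two-part one.

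Second, the primary model adjusts for baseline, which may recover some or all of the shortfall. This also stands as a condition. The article does not say whether SD 3 already reflects the adjustment, so the gain can be neither claimed nor ruled out.

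Third, a reader might infer that the plan carries a 9% family-wise error on top of the power shortfall. The documents do not support that. The 79% and the 9% belong to different success rules. Under the wording that both programmes are superior, each comparison can be tested at 5% without adjustment. The 9% arises only if success in either arm counts and no gate or adjustment is used; the power that goes with that rule is about 95%. The article neither states nor excludes a gate through the F test, and its analysis of variance on three groups followed by comparisons with control is compatible with one. Such detail is commonly left to the SAP, which is not shown.

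A reader might also infer a dropout error, since 90 × 0.85 = 76.5 falls just short of 77. With a rate given only as around 15%, half a subject per group (F-test power 89.8% rather than 90.0%) is not a defect.

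**Conclusion.** The point holds as a mismatch between the sizing and the main hypothesis. The 90% is omnibus power. For the hypothesis that both NVR and PMT are superior to TAU, the same inputs give about 79%, with about 87% for each comparison (78% and 84% if gated by the F test). The probability of missing the main hypothesis is about twice what the 90% suggests.

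These figures assume true differences of exactly 1.5 in both arms, SD 3, 77 evaluable per group, and no precision gain from the baseline covariate. A residual SD of about 2.63 or less would bring joint power to 90%.

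The mismatch does not depend on the unseen SAP, because the hypothesis, the test used for sizing and the power are all fixed in this article. How alpha is handled may depend on the SAP, and inflated type I error is not established.

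**What to change.** Change the wording and add no patients.

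1. In Sample size {14}, label the 90% as the power of the omnibus three-group F test.
2. In Objectives {7} and the primary analysis, state that the main hypothesis is shown only if both comparisons with TAU succeed, each at two-sided 5%, and that no alpha adjustment is then needed.
3. State the power for that rule, about 79% jointly and 87% per comparison, and say whether SD 3 is before or after baseline adjustment. If it is before, any power gain claimed from adjustment should come with its assumed correlation.
4. Only if success on either comparison alone is to count, say so and protect the stated global 5%: test the 2-df treatment effect first and then each comparison at 5%, or use Dunnett-adjusted p-values and intervals. Dunnett is not needed under the both-must-succeed rule, where it would cut joint power from about 79% to about 71%.

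The rule should be fixed before any unblinded comparison is seen. The cost is a few sentences in the protocol and SAP and a less favourable stated power.
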